#### Psychological factors data analysis

In order to determine whether psychological factors can affect acupuncture efficacy, Pearson’s correlation analysis will be performed to assess the relationship between psychological factors and clinical symptom improvement.

#### Mediation analysis

Besides, we will investigate whether the relation between psychological factors and clinical effects of acupuncture are mediated by brain activity by using a method of mediation analysis. In the above analyses, age, gender, and education years will be taken as covariates. The detailed statistical analysis is shown in Fig. 4.

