#### Inclusion criteria

The inclusion criteria include the following: (1) age 45–65 years (male or female), (2) duration of chronic knee pain ≥ 6 months, (3) radiologic confirmation of knee osteoarthritis (Kellgren-Lawrence grade II or III) [26] within 12 months, (4) Numerical Rating Scale (NRS) ≥ 4 with in the past week, (5) right-handed; and (6) written informed consent.

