### Psychological factors evaluation

Psychological factors assessment will include the Mindful Attention Awareness Scale (MAAS), Trait Meta-Mood Scale (TMMS), Big Five Personality (BFP), and Stanford Expectations of Treatment Scale (SETS). MAAS will be used to assess the variations in awareness and attention to present experience [36, 37]. TMMS will be used to assess the capacity to identify emotional states and regulate them [38]. BFP is a widely used personality factors scale, which includes openness, conscientiousness, extraversion, agreeableness, and neuroticism [39, 40]. SETS is a suitable scale to assess individual expectation for upcoming interventions [41]. These psychological factors are relatively stable and not easily modifiable, so they will be only assessed at baseline (Fig. 3). Correlation analyses will be performed to determine the relationships among the brain activity changes, psychological factors, and symptom improvement (Fig. 4).

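### The correlation and mediation analyses of psychological factors compare different patients, but their covariates are fixed at age, gender and education, with no measure of baseline disease severity

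*Protocol article*

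**What the plan says.** The Psychological factors evaluation section lists the instruments: "Psychological factors assessment will include the Mindful Attention Awareness Scale (MAAS), Trait Meta-Mood Scale (TMMS), Big Five Personality (BFP), and Stanford Expectations of Treatment Scale". The personality scale has five dimensions ("which includes openness, conscientiousness, extraversion, agreeableness, and neuroticism"). All are administered at baseline only, so each patient contributes one value per score.

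The Psychological factors data analysis section states its purpose as "In order to determine whether psychological factors can affect acupuncture efficacy". Its method is Pearson's: "correlation analysis will be performed to assess the relationship between psychological factors and clinical symptom improvement". The Neuroimaging data analysis section uses the same coefficient for brain activity against clinical variables. The Mediation analysis section then adds: "we will investigate whether the relation between psychological factors and clinical effects of acupuncture are mediated by brain activity". It closes with the adjustment set for all of these: "In the above analyses, age, gender, and education years will be taken as covariates".

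Severity is established at entry. The Inclusion criteria require at least 6 months of knee pain, an NRS of at least 4 in the past week, and "radiologic confirmation of knee osteoarthritis (Kellgren-Lawrence grade II or III". None of the three appears among the covariates.

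Under Clinical data analysis, the nonspecific effect is the pre-to-post change in the sham phase, and the specific effect is the acupuncture effect minus the sham effect.

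**The concern.** The Study design section justifies the crossover as a control for differences between individuals, psychological factors included. That is right for acupuncture against sham within one patient. It does not carry over to a correlation of a baseline score with improvement, where patients with high scores are compared with other patients who have low scores. There the covariate list is the only protection against confounding, and the article fixes that list instead of leaving it open.

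A patient with worse disease may report lower mood-related scores, show different brain measures and have more or less room for pain to fall. Baseline NRS matters most, because it is itself a component of the NRS change that forms the primary outcome. If severity drives both score and change, the trial can credit a psychological factor with what severity produced, or miss a real association when the two influences have opposite signs. The same error passes into the mediation, which uses the same covariates. At stake is the third objective, on how psychological factors bear on efficacy.

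**Working it through.** The protocol gives no figure for these correlations, so there is none to reproduce. Sample sizes come from the Sample size section: 60 recruited, and 60 x (1 - 0.20) = 48 after the stated 20% attrition. The 5% level is the one named there; two-sided testing is assumed.

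**Step 1: induced correlation.** Let a be the correlation of severity with the score and b its correlation with improvement. If the score has no link of its own with improvement, its marginal correlation is r = a x b. Assumed range for a and b: 0.3 to 0.4.
- Low: 0.3 x 0.3 = 0.09
- High: 0.4 x 0.4 = 0.16

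With a and b of opposite sign, r is -0.09 to -0.16, which offsets a real positive association. That is the masking case.

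**Step 2: chance of significance.** By Fisher's z, the test statistic has mean m = atanh(r) x sqrt(n - 3), and the rejection probability is Phi(m - 1.96) + Phi(-m - 1.96). Here atanh(0.09) = 0.0902 and atanh(0.16) = 0.1614.

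| n | r | m | Rejected at nominal 5% |
|---|---|---|---|
| 48 | 0.09 | 0.605 | 9.3% |
| 48 | 0.16 | 1.083 | 19.1% |
| 60 | 0.09 | 0.681 | 10.5% |
| 60 | 0.16 | 1.218 | 23.0% |

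Allowing for the three planned covariates replaces n - 3 by n - 6. The ranges become 9.0-18.2% (n = 48) and 10.2-22.0% (n = 60), so little changes. The correlations a and b are then read as those remaining after age, gender and education.

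**Step 3: which effect is exposed.** A simulation (5,000 runs per setting, three covariates) used severity correlations of 0.3 or 0.5 with the score and 0.4 or 0.5 with sham-phase change, a wider assumption than in Step 1.

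| Outcome | n = 48 | n = 60 |
|---|---|---|
| Sham-phase change, severity omitted | 11-39% | 14-47% |
| Acupuncture minus sham, severity acting equally in both phases | 4-5% | 4-5% |
| Acupuncture minus sham, severity also modifying the difference (extra slope 0.3) | 9-18% | 10-24% |

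With severity added as a covariate, every setting returned to 3.9-5.6%.

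**Step 4: overlap among scores.** MAAS covers awareness and attention, the personality scale includes neuroticism, and "TMMS will be used to assess the capacity to identify emotional states and regulate them". If one trait truly correlates 0.4 with improvement and an inert score correlates 0.3-0.6 with that trait, the inert score shows r = 0.12 to 0.24. By the Step 2 formula it is significant in 12.8-37.5% of trials at n = 48 and 14.9-45.6% at n = 60.

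Mutual adjustment has a price. With overlap 0.6, the true trait's partial correlation is (0.40 - 0.24 x 0.60) / sqrt[(1 - 0.24^2)(1 - 0.60^2)] = 0.256 / 0.777 = 0.33. Its power at n = 48 falls from 81% (r = 0.40, n - 3) to 62% (r = 0.33, n - 4).

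**The case against.** **The study is exploratory.** It calls itself a pilot, and the third objective is framed as exploration. This stands and lowers the weight of the point. It does not remove it, because the analysis section states a purpose of settling whether these factors affect efficacy.

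**The specific effect is a within-patient difference.** This stands. Severity that acts equally in both phases cancels. A reader might infer that all the psychological analyses are confounded by severity; the definitions in the protocol do not support that.

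**Pearson's coefficient and covariates.** A reader might infer that the planned analysis cannot be run, because a simple Pearson coefficient takes no covariates. The covariate sentence refers back to the preceding analyses, so partial correlation is the natural reading. Only the name needs settling.

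**Overlapping scores.** A reader might infer that single-score correlations are invalid and that effects should be attributed only from mutually adjusted coefficients. The documents do not support that. The text does not say whether scores enter the mediation singly or together, and the figure said to hold the detail is not reproduced. If one trait acts through another, mutual adjustment removes part of a real effect, and Step 4 shows the loss of power. A joint model therefore serves as a sensitivity analysis, not a replacement.

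**The size is assumed.** This stands. No correlation among severity, scores and improvement is given, so the percentages illustrate and do not predict.

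**Conclusion.** The point holds as a shortcoming in the choice of covariates. The list is fixed in the text, the comparisons it serves are between patients and non-randomised, and it leaves out severity values already obtained at entry. The exposure is mainly in the nonspecific and total effects. Under assumed severity correlations of 0.3-0.4 with both variables, the false-positive rate is about two to four times nominal with 48 patients (9-19%) and up to nearly five times with 60 (10.5-23%). For the specific effect the rate stays nominal unless severity modifies the acupuncture-sham difference. If severity is nearly unrelated to the scores or to improvement, the bias is negligible, but nothing in the protocol establishes that. The acupuncture-sham comparison itself is not affected. The change is worth making before analysis; it is not a reason to doubt the design.

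**What to change.** In the Mediation analysis section:

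- Extend the covariates for the correlation and mediation analyses to age, gender, education years, baseline NRS, Kellgren-Lawrence grade (II or III) and pain duration.
- Name the method as partial correlation or linear regression, here and in the two sections that now say Pearson's correlation.
- Beside the single-score analyses, add one sensitivity regression per effect with a small prespecified set of psychological scores entered together. With 48-60 patients and at least eight scores (five personality dimensions plus one each from the other three scales), the full set would strain the model.
- Word single-score results as associations with improvement, not as effects of that factor.

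The cost is analysis wording only, since the variables are already available. Three more degrees of freedom are used. In the joint model, overlapping scores have wider intervals: the variance inflation 1 / (1 - overlap^2) for a pair is 1.33 at a correlation of 0.5 and 1.56 at 0.6.

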### Ethics and dissemination

The protocol has been approved by the local ethical committees of Dongzhimen Hospital Affiliated to Beijing University of Chinese Medicine (reference: DZMEC-KY-2017-53-02) and registered in Chinese Clinical Trial Registry (reference: ChiCTR1900025807). We will conduct the study according to the principles of the Declaration of Helsinki. Written informed consent will be obtained before randomization from all patients. The results will be published in the peer-reviewed journal and presented at conference presentations.

## Discussion

To the best of our knowledge, this is the first study to evaluate the neurological and psychological mechanisms of specific and nonspecific effects of acupuncture. A crossover trial is an ideal design for clinical, psychological, and neuroimaging studies, because it can improve the accuracy of effect estimation by assessing the effects of different interventions for each patient. In our study, to further understand and identify the specific and nonspecific effects of acupuncture, alternations in cerebral activities and differences in psychological factors will be observed during the acupuncture intervention for patients with KOA. By combing clinical and psychological measurements and neuroimaging analysis, acupuncture effects and related neural and psychological changes can be tracked longitudinally.

Indeed, the clinical efficacy of acupuncture depends on comprehensive functions of physiology and psychology [49]. Psychological factors play an important modulatory role during acupuncture intervention [50]. The specific effect is the biological effect produced by its nature [3], while the nonspecific effect may be mainly mediated by such psychological factors as expectation, personality, awareness, and emotion. Both of them could contribute to the effects of acupuncture [16, 17]. However, plenty of previous studies focused on capturing the total or specific effects of acupuncture, while ignoring the nonspecific effect. Consequently, few studies tended to evaluate and differentiate the specific and nonspecific effects. And our study could exactly fill the vacancy regarding the mechanism of the specific and nonspecific effects of acupuncture.

Whether the clinical effect of acupuncture is equivalent to placebo acupuncture has always been the focus of debate. However, it is undeniable that the nonspecific effect of acupuncture is an important part of the clinical effects [51]. In fact, clinical practice desires to explicitly understand the maximum potential of an intervention. And there is an interest in optimizing nonspecific effect of acupuncture to enhance existing clinical effects. Hence, a better comprehending of the neurological and psychological mechanisms of specific and nonspecific effects of acupuncture is essential to achieve these aims. Our study will contribute to explore the maximum potential of acupuncture.

## Trial status

The Ethical Committee of Dongzhimen Hospital Affiliated to Beijing University of Chinese Medicine approved the study protocol on 29 August 2019 (version 2.0, 25 June 2019). This trial is currently recruiting patients and the first patient was included in 30 October 2019. We predict that recruitment will be completed by December 2021.

## Data Availability

The datasets analyzed during the current study are available from the corresponding author on reasonable request.

## Abbreviations

NRS: Numerical Rating Scale
WOMAC: Western Ontario and McMaster Universities Osteoarthritis Index
SF-MPQ: Short form McGill pain questionnaire
BFP: Big Five Personality
MAAS: Mindful Attention Awareness Scale
TMMS: Trait Meta-Mood Scale
SETS: Stanford Expectations of Treatment Scale
fMRI: Functional magnetic resonance imaging
NA: Non-acupoint
KOA: Knee osteoarthritis
CRF: Case report form
ITT: Intention-to-treat analysis
LOCF: Last observation carried forward
